#### **7.1.7 Follow-up of AEs**

AEs, especially those for which the relationship to investigational product is suspected, should be followed up until they have returned to baseline status or stabilized.

If after follow-up, return to baseline status or stabilization cannot be established an explanation should be recorded in the study record.

### **7.2 Vital Signs**

In office, seated resting blood pressure and heart rate will be determined from a single measurement. Blood pressure will be checked in both arms at the first examination. If a consistent interarm difference exists, the arm with the higher pressure will be used throughout the study. One arm will be chosen and used consistently throughout the study. The arm selected for use at the initial visit will be documented in the study file.

Prior to blood pressure measurements, subjects will be encouraged to use the restroom. The subject should be seated comfortably with the back supported and the upper arm bared without restrictive clothing. Feet should be flat on the floor, legs should not be crossed. The subject should rest in this position for at least 5 minutes prior to the reading and must not talk during the measurement.

The same recording method and the same equipment should be used for each subject throughout the study.

### **7.3 Biometrics**

Height will be measured at baseline with shoes removed and back straight using a stadiometer. Height will be measured in centimeters to one decimal place (e.g. 182.3 cm). Height will only be measured at screening. Two separate measurements of height will be taken and averaged. If height varies more than 1 cm, a third measurement will be taken. The closest two measurements will be used for the final calculation of height.

Weight will be measured at every study visit using a beam scale. Two separate measurements of weight will be taken and averaged. If weights vary more than 0.5 kg, a third measurement will be taken. The closest two measurements will be used for final calculation of weight. Weight will be measured with subjects in light clothing.

Body mass index will be calculated as  $[\text{weight (kg)}] \div [\text{height (m)}^2]$  using the weight (kg) at each visit divided by the square of the height (m) measured at visit 1. BMI will be recorded to one decimal place with the units  $\text{kg/m}^2$ .

Measurements of height, weight and BMI will be rounded to the nearest tenth using standard rounding conventions (e.g. a value of 0.50 or greater [0.50 to 0.99] rounds up to the next whole number and anything less than 5 [0.49 to 0.00] rounds down). For example an average height of 182.35 cm will be rounded to 182.4 cm.

## **7.4 Hematology and Clinical Chemistry**

Fasting (12 hours) blood samples will be collected at screening (Visit 1) and week 12 (Visit 6) at the end of the treatment period. Samples will be analyzed for complete blood count (CBC) with differential (hemoglobin, hematocrit, white blood cell count with differential, red blood cell count and platelet count), BUN, creatinine, eGFR, AST, ALT, and electrolytes (Na, K, Cl).

# **8 STATISTICS**

Values of all primary and secondary variables will be summarized using descriptive statistics for all treatments. Safety analyses will include, where appropriate, descriptive statistics, counts and percentages.

## **8.1 Planned Interim Analysis**

When approximately 100% of participants have completed Visit 3 (Day 28), an interim analysis to determine changes in serum phospholipid fatty acids will be performed by research staff not involved in the conduct of the clinical trial.

## **8.2 Sample Size**

For this study, twenty four (24) subjects per group are expected to complete the study. With an expected attrition rate of 20%, thirty (30) subjects per group are required for this study. A formal sample size was not done for this investigative study.

## **8.3 Analytical Populations**

### **8.3.1 Intent-To-Treat Population**

Any subject known to start treatment (known to have taken  $\geq 1$  dose of study product) and completing at least one post-baseline visit will be included in the analysis of efficacy (intention-to-treat population).

### **8.3.2 Safety Population**

Any subject known to start treatment (known to have taken  $\geq 1$  dose of study product) will be included in the analysis of safety.

## **8.4 Statistical Methods**

An effectiveness analysis based on the intent-to-treat population will be performed for all efficacy outcomes. Continuous variables will be presented as means with standard errors of the mean (SEM). Categorical variables will be shown as frequencies or proportions. Numerical efficacy endpoints will be

formally tested for significance by analysis of covariance. The dependent variable will be the post-baseline value; the factor of interest will be the treatment group (product) and value at baseline (usually visit 2, except for some laboratory tests [e.g. lipid profile] where baseline is visit 1) will be the covariate.

The ANCOVA approach differs from the simpler approach of comparing changes from baseline between products in that the ANCOVA adjusts for baseline in a more sophisticated way than simply subtracting it from the end of study value. The adjustment allows the ANCOVA to compensate for regression to the mean, floor effects, and other ways that the baseline value could influence change from baseline.

Where values being summarized as significantly non-normally distributed, as assessed by the Anderson-Darling test, a non-parametric test, such as the Wilcoxon or Mann-Whitney U test will be used.

A within-group analysis, if warranted, may be performed using a Student's paired samples t-test or Wilcoxon sign rank test.

All calculations and analyses will be performed using SAS version 9.2 or higher. For all statistical inferences, the tests will be performed at the two-sided, 0.05 level of significance.

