### **5.2 Description of IP**

The investigational product (IP) is Ultimate Omega® [NPN 80003338]

Manufacturer: Nordic Naturals Inc.

Formulation of the IP (per capsule):

Medicinal Ingredients: Fish Oil 1000mg (providing 325mg EPA, 225mg DHA and 90mg other Omega-3 Fatty Acids)

Non-medicinal ingredients: Gelatin, Glycerin, Natural Lemon Flavour, Rosemary extract, Water

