### **5.1 Description of Comparator Product**

The comparator product is Meg-3™ Formulation of the comparator product (per capsule):

Medicinal Ingredients: Fish Oil 1000mg (providing 300mg EPA and 200mg DHA)

Non-medicinal ingredients: Gelatin, Purified Water, Natural Lemon Flavour, Rosemary extract and Vitamin E

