## 5.3 Dosage and Administration of IP

Subjects will be instructed to take the investigational product as 5 capsules in the morning with food on a daily basis for 168 days.

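### The efficacy ANCOVA adjusts only for the endpoint's own baseline; adding sex and Visit 2 body weight could modestly improve precision at little cost

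*Protocol*

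**What the plan says.** Section 8.4 (Statistical Methods) describes the efficacy ANCOVA: "The dependent variable will be the post-baseline value; the factor of interest will be the treatment group (product) and value at baseline", the latter entering as the covariate. The synopsis gives the same model. For most endpoints baseline is Visit 2; for the lipid profile it is Visit 1. No other term is named, and "the tests will be performed at the two-sided, 0.05 level of significance".

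Four other parts of the protocol bear on this:

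- **Dose.** Section 5.3 has every participant "take the investigational product as 5 capsules in the morning with food on a daily basis for 168 days". The number of capsules does not depend on body weight.
- **Weight.** Section 7.3 states: "Weight will be measured at every study visit using a beam scale". The Visit 2 procedures list weight ahead of randomisation.
- **Sex.** Section 3.3 (Allocation to Treatment) plans 15 men and 15 women in each arm, and section 5.1 (Treatment Groups) repeats the balance.
- **Size.** Section 8.2 says "twenty four (24) subjects per group are expected to complete the study" and that no formal sample size calculation was done.

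**The concern.** With a fixed capsule count, a lighter participant receives more EPA and DHA per kilogram than a heavier one. The BMI limits of 18.5 to 24.9 kg/m² restrict weight but do not fix it, because weight also rises with height and both sexes are enrolled. If body weight or sex predicts the fatty acid response after adjustment for baseline, that variation stays in the error term and the interval for the product difference is wider than it need be.

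Balancing sex between the arms prevents a sex imbalance, but it does not take the between-sex variance out of the error term; only a model term does that. In a trial of 30 per arm with no stated power, precision that can be had from data already collected is worth taking. What is at stake is the width of the interval, not the validity of the test.

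**Working it through.** **The plan's own figure.** Section 8.2 states: "With an expected attrition rate of 20%, thirty (30) subjects per group are required for this study". 24 / (1 − 0.20) = 30 per arm, which reproduces. No power, effect size or SD is given, so there is no power figure to check.

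**Dose contrast.** The investigational capsule is "Fish Oil 1000mg (providing 325mg EPA, 225mg DHA and 90mg other Omega-3 Fatty Acids"; the comparator is "Fish Oil 1000mg (providing 300mg EPA and 200mg DHA".
- Investigational product: 5 × (325 + 225) = 2750 mg EPA + DHA a day.
- Comparator: 5 × (300 + 200) = 2500 mg a day.
- Ratio: 2750 / 2500 = 1.10. By fatty acid, EPA is 325 / 300 = +8.3% and DHA is 225 / 200 = +12.5%.

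**Spread of body weight within the BMI limits.** Weight = BMI × height².
- At any one height the range is 24.9 / 18.5 = 1.35-fold.
- With heights of 1.55 to 1.90 m (assumed), the extremes are 18.5 × 1.55² = 44.4 kg and 24.9 × 1.90² = 89.9 kg. On the investigational product that is 2750 / 44.4 = 61.9 down to 2750 / 89.9 = 30.6 mg/kg a day.
- A simulation with BMI uniform over its range and assumed heights (men 1.77 m, SD 0.07; women 1.64 m, SD 0.065) gives an SD of log weight of about 0.14 overall and 0.12 within sex. Weight therefore varies within each sex too.

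**Effect on the interval.** With 48 completers, the planned model (intercept, product, baseline) leaves 48 − 3 = 45 error degrees of freedom. Adding weight leaves 44; adding weight and sex leaves 43. Let R² be the share of the planned model's residual variance that the added terms explain. With the arms balanced on the added terms,

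width ratio = √[(1 − R²) × 45 / df] × t(df) / t(45),

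where t is the 97.5% point: t(45) = 2.0141, t(44) = 2.0154, t(43) = 2.0167.

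| R² (assumed) | Weight alone, df 44 | Sex and weight, df 43 |
|---|---|---|
| 0 | 1.012 | 1.024 |
| 0.05 | 0.986 | 0.998 |
| 0.10 | 0.960 | 0.972 |
| 0.15 | 0.933 | 0.944 |

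Example: sex and weight at R² = 0.10 give √(0.90 × 45 / 43) × 2.0167 / 2.0141 = 0.972, an interval 2.8% narrower.

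**Break-even.** The terms pay for themselves once R² exceeds 1 − 1/1.0119² = 2.3% for weight alone, or 1 − 1/1.0243² = 4.7% for the pair.

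**Two cautions in reading the table.** The columns share R² values only to show the price of the second degree of freedom; sex and weight together cannot explain less than weight alone. And a chance weight imbalance widens the adjusted interval a little more: at one standard error, the squared correlation of weight with arm is about 1 / (1 + 46) = 0.021, and 1 / √(1 − 0.021) = 1.011, so about 1%.

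**The case against.** The strongest reply is that nothing in section 8.4 is an error. A baseline-adjusted ANCOVA is a sound model for a randomised trial: it is unbiased and its type I error is controlled. Further prognostic covariates are often named in a statistical analysis plan, which may exist but was not available here. The documents also give no evidence that body weight predicts red cell or serum phospholipid EPA and DHA after baseline adjustment, so even the sign of the change in interval width is undetermined. All of this stands, and it limits the point to an optional refinement. It does not remove it, because the protocol states a specific model rather than leaving the covariates open, and that model omits the variable on which allocation is balanced.

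A reader might go further and infer that a chance weight imbalance could rival the product contrast. The documents do not support that. With a within-sex weight SD of 7.4 kg (assumed), the standard error of the between-arm difference is 7.4 × √(2/30) = 1.9 kg, about 3% of a mean weight near 63 kg (simulated). An imbalance of two standard errors is about 6%. It would be uncommon, it falls short of the 10% EPA + DHA contrast, and it shifts the estimate by 6% only if response is proportional to dose per kilogram. The ordinary ANCOVA standard error already allows for such imbalance. Moreover, section 2.1 frames the objective as comparing two forms of fish oil, not as detecting a 10% dose difference.

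A reader might also set the 31 to 62 mg/kg range against that 10%. The range describes individuals at the extremes of height and BMI; the 10% is a contrast between arms. The two are not comparable.

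**Conclusion.** The point holds as a modest improvement in precision. The planned analysis is neither biased nor invalid, and a reader should not infer otherwise. With 48 completers, adding sex and Visit 2 weight moves the 95% interval between about 2.4% wider (nothing explained) and 5.6% narrower (15% explained), with break-even near 5%. For weight alone the range is 1.2% wider to 6.7% narrower.

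These figures assume 48 analysed participants and balance on the added terms. The analysed number may differ from 48 under the intent-to-treat definition in section 8.3.1 and the carrying forward of last values in section 8.6. The share of variance explained is unknown from the documents, so confidence in the size of any gain is low. The priority is low: worth doing if the model is being revised, but not a reason to question the trial.

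**What to change.** In section 8.4 and the synopsis, or in the statistical analysis plan before unblinding, pre-specify sex and Visit 2 body weight as further terms in the ANCOVA for the red cell and serum phospholipid fatty acid endpoints, alongside the baseline value. If only one term is to be added for its expected precision, weight alone costs less; the separate reason for including sex is that the allocation is balanced on it.

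The cost is two degrees of freedom (45 to 43), or one for weight alone. No new measurement, visit or participant is needed, and dosing is untouched. The terms should be fixed before treatment codes are known, so that their inclusion cannot look data-driven.

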### 3.3 Allocation to Treatment

Each participant will be randomized in a 1:1 to ratio to either the investigational product (Ultimate Omega®) or comparator product Meg-3™ as follows:

| Study Arm       | Subject Number                 |
|-----------------|--------------------------------|
| Ultimate Omega® | N=30 (15 Males and 15 Females) |
| Meg-3™          | N=30 (15 Males and 15 Females) |
| Total    | 60                      |

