## **4 SELECTION AND WITHDRAWAL OF SUBJECTS**

### **4.1 Number of Study Volunteers**

Sixty (60) participants will be enrolled in this study, with equal numbers of male and female subjects assigned to each group.

Subjects will be recruited for this study from the Guelph, Ontario region located in Southwestern Ontario, Canada. Advertisement of the study will include using NDI's electronic subject database to identify potential candidates, e-mail and online advertisement, and posted paper advertisements. Participants interested in the study will contact the study recruiters via phone, e-mail or online. Following this first contact, the study will be discussed in more detail and additional information not found on the recruitment material will be provided. Following this conversation, potential participants will schedule a first study visit appointment. During this appointment, further questions or concerns about the study will be addressed and subjects will read the informed consent. Subjects will be given the opportunity to take the informed consent home to consider participating in the study and respond to the recruiter, or alternatively, subjects may sign and agree to participate in the study immediately. Once the informed consent is obtained, subjects will be screened against the inclusion/exclusion criteria to determine whether they may participate in the study.

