## **5 INVESTIGATIONAL PRODUCT**

### **5.1 Treatment Groups**

The study will consist of two treatment groups. Participants will be randomly assigned, in equal proportions, to the two treatment groups. An equal number of male and female subjects will be randomized to each group. Alpha-numerical codes will be used to identify participants. At randomization each subject will receive a unique numerical randomization code.

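### Allocation is balanced by sex within each arm, but the stated efficacy ANCOVA leaves sex out; if sex predicts the outcome beyond baseline, precision is lost and the test is conservative

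*Protocol*

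**What the plan says.** Three sections of the protocol fix the sex composition of the arms. Section 3.3 (Allocation to Treatment) gives each arm "N=30 (15 Males and 15 Females" within a 1:1 allocation. Section 4.1 describes 60 participants "with equal numbers of male and female subjects assigned to each group". Section 5.1 (Treatment Groups) states: "An equal number of male and female subjects will be randomized to each group". The word stratified is not used, but fixed counts of men and women within arm are balance by design.

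Section 8.4 says that numerical efficacy endpoints will be "formally tested for significance by analysis of covariance". The post-baseline value is the dependent variable, and the model terms follow: "the factor of interest will be the treatment group (product) and value at baseline", with baseline named as the covariate, in the singular. The Statistical Methods entry of the synopsis gives the same model. For non-normal data, 8.4 falls back on a Wilcoxon or Mann-Whitney test, again without sex. The significance level is set by "the tests will be performed at the two-sided, 0.05 level of significance".

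No section adds sex to any efficacy analysis.

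**The concern.** Balancing on a factor helps precision only if the analysis knows about it. With equal numbers of men and women in both arms, a male-female difference in outcome cancels out of the product comparison, so the true sampling variance of that comparison does not contain it. A model without sex still counts the difference as residual noise. The reported standard error then exceeds the true one, the confidence interval is wider than it need be, and the real significance level lies below the nominal 5%.

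Precision matters in this trial. Section 8.2 says "twenty four (24) subjects per group are expected to complete the study", with no formal sample size calculation. The two products are similar active fish oils (325 mg EPA and 225 mg DHA per capsule against 300 mg and 200 mg), so a difference may be small. Section 10.2 speaks of showing bioequivalence or superiority, and needlessly wide intervals make either harder.

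**Working it through.** **Inputs from the protocol.** Two-sided alpha 0.05 and the model terms (8.4); 1:1 allocation with 15 men and 15 women per arm (3.3); 24 expected completers per arm and 20% attrition (8.2).

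**The plan's own figure.** 24 / (1 − 0.20) = 30 per arm, 60 in total. This reproduces. The protocol states no power, effect size or SD, so there is no power figure to reproduce.

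**Assumption.** The protocol gives no effect of sex on the outcome after baseline adjustment. Let R² be the share of the residual variance (after baseline) that sex explains. The assumed range is 0 to 30%, and zero is included deliberately.

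**Formulas.** With a 50:50 split, a male-female difference of g within-sex SDs adds g²/4 to a within-sex residual variance of 1. So R² = (g²/4)/(1 + g²/4), and g = 2√(R²/(1 − R²)).

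- Overstatement of the standard error when sex is omitted and balanced: 1/√(1 − R²).
- Actual alpha with N subjects in total: 2·P(T > t·k), where t is the 0.975 quantile on N − 3 df, T has N − 4 df, and k = √(1 + (g²/4)·N/(N − 1)).

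**Example, R² = 20%, 24 per arm (N = 48).** g = 2√(0.2/0.8) = 1.00. The standard error ratio is 1/√0.8 = 1.118. k = √(1 + 0.25·48/47) = 1.120, and t on 45 df is 2.014. The product is 2.257, whose two-sided tail on 44 df is 0.029.

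| Residual variance explained by sex | Sex difference g (within-sex SD) | SE overstated by | Actual alpha, 24 per arm |
|---|---|---|---|
| 0% | 0 | 0% | 5.0% |
| 5% | 0.46 | 2.6% | 4.5% |
| 10% | 0.67 | 5.4% | 3.9% |
| 20% | 1.00 | 11.8% | 2.9% |
| 30% | 1.31 | 19.5% | 2.0% |

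At 30 per arm the alpha values agree to within 0.1 point.

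**Check by simulation** (40,000 null trials and 20,000 under the alternative per setting; sex equal in both arms; assumed baseline slope 0.6):

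- With sex in the model, alpha stayed between about 0.047 and 0.051 in every setting, at 24 and at 30 per arm.
- Without sex at 24 per arm, alpha was 0.0495 at g = 0, 0.043 at g = 0.5 and 0.028 at g = 1.0.
- Power at 24 per arm, for a product difference of 2.8·√(2/24) = 0.81 within-sex SD, with against without sex: 76.9 vs 77.0% at g = 0; 77.7 vs 75.8% at g = 0.5; 77.4 vs 69.4% at g = 1.0.
- When sex was not balanced between arms by design (30 per arm), the model without sex kept its level: 0.050 at g = 0.5 and 0.048 at g = 1.0. The conservatism therefore comes from the forced balance combined with the missing term.

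**Loosened balance.** If six of 30 are lost at random in each arm, alpha without sex at the 20% setting is about 3.3%, against 2.9% with exact balance.

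**The case against.** The strongest objection is that the consequence is conditional. A reader might infer from the mismatch alone that the error term is too large and the level below 5%. The documents do not support that, because they give no sex effect, and with no residual sex effect nothing changes. This stands, and the point is worded accordingly.

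The upper end of the range also needs a large effect. A 20% share means a full 1 SD difference between men and women after adjustment for the same analyte's baseline, which absorbs much of any standing difference in level. The sample is narrow as well (healthy, 18 to 35 years, BMI 18.5 to 24.9). A reader might infer that the omission costs about a fifth of the sample. In terms of interval width that is the arithmetic at 20% (1 − 0.20 = 0.80), but nothing in the protocol shows that 20% applies.

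Balance is fixed at randomization, not at analysis. Under 8.3.1 and 8.6 the efficacy set is everyone treated with at least one post-baseline visit, with last observation carried forward. The analysed number is thus likely to lie nearer 30 than 24 per arm, and its balance may be slightly off. This weakens the effect a little but does not remove it.

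Finally, covariates are often settled in a statistical analysis plan, and one may exist. That does not answer the point: the protocol does not leave the model open, but names its factor and its single covariate. An analysis plan that added sex would depart from that text.

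**Conclusion.** The stated model leaves out a factor on which the allocation is balanced. If sex predicts the outcome beyond baseline, the standard error is overstated, by about 3 to 20% when sex explains 5 to 30% of the residual variance, and the actual alpha falls to about 4.5 to 2.0%. If sex does not predict it, the effect is nil. The loss of power is about 2 points at a sex difference of 0.5 SD and 8 points at 1 SD. These figures assume near-exact balance by sex in the analysed set, and the sex effect itself is an assumption.

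The point concerns efficiency and calibration. A reader might infer that the trial's conclusions are put at risk. They are not: the product estimate is unbiased, false positives are not inflated, and the protocol makes no power claim that the omission could break. The change is still worth making, because the cost is negligible if sex is irrelevant and the gain is material if it is not.

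**What to change.** In 8.4 and in the Statistical Methods entry of the synopsis, specify the efficacy ANCOVA as product + baseline value + sex, with sex as a fixed factor. Where the rank-test fallback is used, replace the plain Wilcoxon or Mann-Whitney test with its sex-stratified form (van Elteren), since a term cannot simply be added to a rank test. Any statistical analysis plan should carry the same terms.

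The cost is one phrase in each place and one degree of freedom (44 instead of 45 with 24 per arm). Sex is already known for every participant, so no further data are needed.

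### Section 8.4 tests normality on the values rather than the ANCOVA residuals, and its named fallback tests drop the baseline adjustment that the section gives as its reason for ANCOVA

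*Protocol*

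**What the plan says.** Section 8.4 says that numerical efficacy endpoints will be "formally tested for significance by analysis of covariance". It specifies the model: "The dependent variable will be the post-baseline value; the factor of interest will be the treatment group (product) and value at baseline" (the last as covariate). It explains why this is preferred to comparing changes: "The adjustment allows the ANCOVA to compensate for regression to the mean, floor effects, and other ways" in which baseline could act.

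A later paragraph of the same section adds a switch. The trigger is "Where values being summarized as significantly non-normally distributed, as assessed by the Anderson-Darling test", and the consequence is that "a non-parametric test, such as the Wilcoxon or Mann-Whitney U test will be used". The rule does not mention model residuals. For the replacement test it gives no covariate, transformation or rank adjustment, and it does not say whether post-baseline values or changes would be ranked.

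The Statistical Methods row of the synopsis gives ANCOVA with no switch. Section 8.5 also applies ANCOVA to the safety laboratory values with no switch.

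**The concern.** ANCOVA relies on roughly normal residuals. The values themselves also carry the spread of the baseline, which the model removes, so they can fail a normality test when the model is sound.

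Once the switch is made, the named tests compare the arms without baseline, and the section's own argument for ANCOVA no longer applies to that endpoint. The target changes too. ANCOVA estimates an adjusted mean difference, while Mann-Whitney concerns the chance that a value in one arm exceeds one in the other. Which of these is tested depends on the observed data.

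The trial may have little power to spare. The labelled contents differ by 325 − 300 = 25 mg EPA and 225 − 200 = 25 mg DHA per capsule, and Section 8.2 states that no formal sample size calculation was done.

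**Working it through.** **Inputs from the protocol.** Section 8.2: "twenty four (24) subjects per group are expected to complete the study". Section 8.4: "the tests will be performed at the two-sided, 0.05 level of significance". Allocation is 1:1 (Allocation to Treatment).

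**Assumed, because the protocol gives no figure.** True difference of 0.6 SD of the post-baseline value; correlation ρ between baseline and post-baseline value of 0.3 to 0.8; the shapes of the distributions; Anderson-Darling applied to the pooled values at 0.05; Mann-Whitney applied to post-baseline values.

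**The plan's own figure.** 24/(1 − 0.20) = 30 per group, which reproduces exactly. No power is stated.

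**If the switch always happened, with normal data.** Efficiency of Mann-Whitney relative to ANCOVA is (3/π)(1 − ρ²).
- ρ = 0.3: 0.955 × 0.91 = 0.87, so 24 per arm work like about 21.
- ρ = 0.5: 0.955 × 0.75 = 0.72, like about 17.
- ρ = 0.7: 0.955 × 0.51 = 0.49, like about 12.

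ANCOVA power is Φ(0.6/[√(1 − ρ²) × √(2/24)] − 1.96), and 0.6/√(2/24) = 2.08. This gives 0.59, 0.67 and 0.83 at ρ = 0.3, 0.5 and 0.7. For Mann-Whitney, 2.08 × √0.955 = 2.03, and Φ(2.03 − 1.96) = 0.53 at every ρ.

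**The two-stage rule as written.** Simulation with 24 per arm and 3,000 trials per row: ANCOVA unless the values fail Anderson-Darling, otherwise Mann-Whitney. Skewed variables are log-normal with log-scale SD 0.6. The last column is two-stage minus ANCOVA, in percentage points.

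| Data | ρ | Switch rate | ANCOVA | Two-stage | Rank ANCOVA | Change |
|---|---|---|---|---|---|---|
| Normal | 0.3 | 5% | 0.557 | 0.554 | 0.544 | −0.3 |
| Normal | 0.5 | 4% | 0.637 | 0.630 | 0.601 | −0.7 |
| Normal | 0.7 | 5% | 0.821 | 0.808 | 0.770 | −1.3 |
| Normal | 0.8 | 4% | 0.913 | 0.894 | 0.868 | −1.9 |
| Skewed baseline, normal errors | 0.3 | 5% | 0.558 | 0.555 | 0.538 | −0.3 |
| Skewed baseline, normal errors | 0.5 | 8% | 0.636 | 0.626 | 0.589 | −1.0 |
| Skewed baseline, normal errors | 0.7 | 20% | 0.794 | 0.736 | 0.735 | −5.8 |
| Skewed baseline, normal errors | 0.8 | 33% | 0.918 | 0.795 | 0.864 | −12.3 |
| Skewed baseline and errors | 0.3 | 73% | 0.598 | 0.709 | 0.761 | +11.1 |
| Skewed baseline and errors | 0.5 | 67% | 0.679 | 0.720 | 0.798 | +4.1 |
| Skewed baseline and errors | 0.7 | 63% | 0.834 | 0.748 | 0.878 | −8.6 |
| Skewed baseline and errors | 0.8 | 65% | 0.903 | 0.741 | 0.927 | −16.2 |

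A separate simulation, also with 24 per arm and a 0.6 SD difference, gave falls at ρ = 0.8 from 0.92 to 0.82 (skewed baseline) and from 0.91 to 0.77 (skewed baseline and errors). Together the two give about 10 to 16 points.

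**Is the switch needed?** With a skewed baseline and normal errors, residuals fail in about 5% of trials at every ρ, while values fail in 5% to 41% across ρ = 0.3 to 0.8 (with and without a treatment difference). With skewed errors, residuals fail in about 90% of trials, yet ANCOVA's type I error stays at 3.7% to 4.5%.

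**Type I error of the two-stage rule.** 4.1% to 5.7% across all scenarios. The simulation error is √(0.05 × 0.95/3000) = 0.4 points.

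**The case against.** The strongest reply has four parts.

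1. **The wording is open.** The tests are introduced as examples, and ranking changes from baseline is not excluded. For normal data at ρ = 0.7, Mann-Whitney on changes has power 0.73 against 0.82 for ANCOVA, and with skewed errors at ρ = 0.7 it reaches 0.89 against 0.83. This stands as a caution on the size of the loss. But at ρ = 0.3 with normal data it drops to 0.37 against 0.56, and it is the change-score approach that Section 8.4 calls simpler than ANCOVA. Leaving the choice open adds a decision after the data are seen.

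2. **The correlation may be low.** Exclusions E2 and E3 remove n-3 supplement users and frequent eaters of oily fish, and everyone takes five capsules a day. That may narrow the baseline spread and lower ρ. This stands: at ρ = 0.3 the rule loses almost nothing, and with skewed errors it gains.

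3. **Non-normal values often mean non-normal residuals.** This stands for skewed errors. A reader might infer that the switch happens often for no valid reason. The protocol gives no figure for that, and the rate runs from about 5% with normal data to about 40% only under a skewed baseline, normal errors and ρ = 0.8.

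4. **Details may sit in a SAP that is not at hand.** Diagnostics and interval reporting could be there, so their absence from the protocol is not counted. Nor does the protocol say outright that the rule is applied visit by visit. The trigger and the replacement, however, are stated in Section 8.4 itself.

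**Conclusion.** The point holds as a defect in a stated rule. The normality check is on the wrong quantity, and the named fallback tests undo the section's own justification for ANCOVA.

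The size is uncertain. Under the assumptions above, the loss of power is negligible to small for normal data or low correlation, 6 to 9 points with skewed data at ρ = 0.7, and about 10 to 16 points with skewed data at ρ = 0.8. With skewed errors at ρ = 0.3 and 0.5 the rule beats ANCOVA on the raw scale, but rank ANCOVA beats both.

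Two stronger readings are not supported. A reader might infer that pre-testing raises the false-positive rate, but the simulations show no inflation. A reader might also take the efficiency of 0.49 as the trial's loss, but that figure applies only if the switch always happens, at ρ = 0.7, on normal data where it happens in about 5% of trials. The validity of the tests survives. What is at risk is power, and a test and estimand fixed in advance.

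**What to change.** Rewrite the non-normality paragraph of Section 8.4:

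- Baseline-adjusted ANCOVA is the analysis for every numerical efficacy endpoint, whatever a normality test on the values shows.
- Normality is judged on the model residuals.
- The Wilcoxon/Mann-Whitney fallback is replaced by one that keeps baseline: a log transformation pre-specified for named variables expected to be right-skewed, or rank ANCOVA (ranked outcome on ranked baseline and product) as a sensitivity analysis.

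The cost is one paragraph, slightly more analysis work and a less familiar fallback test. Rank ANCOVA gives up some power when data are normal (0.770 against 0.821 at ρ = 0.7), which is why it serves as a sensitivity analysis and not as the main test. No extra data or participants are needed.
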